##### Complications

Complications will be assessed at every outpatient visit and after 2 years. They will include infection, nonunion, implant failure, complex regional pain syndrome, and any adverse event needing surgical intervention. For patients treated surgically, the need for implant removal will also be recorded. Infections will be defined according to the guidelines of The Centers for Disease Control and Prevention and subdivided into superficial incisional and deep infections. Deep infections will include both deep incisional and organ or space infections [5]. The diagnosis of complex regional pain syndrome is based on the Budapest clinical diagnostic criteria [12]. Nonunion is defined as a Radius union scoring system score greater than or equal to 6. It will be assessed 1 year after injury. The RUSS score evaluates union on dorso-volar and lateral radiographs by assigning a score of 0 to 2 on each cortex. Zero points are given if the fracture line is visible with no callus, 1 point if a callus is present but the fracture line is still visible, and 2 points if the fracture line is not visible and a bridging callus is present. In surgically treated cases, where the cortex is not visible due to the implant, a score of 0 is given to that cortex [13]. In case of doubt with regard to union, a computer tomography scan will be acquired. Patients with nonunion will be divided into 2 groups based on their symptoms (symptomatic vs asymptomatic).

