## Methods

### Study Design

Although randomized controlled trials are generally considered the gold standard to investigate the effects of medical treatments, both patients and surgeons can have a strong preference for a certain treatment, which may limit the feasibility of a randomized controlled trial and therefore the generalizability of its results [4,5]. Provided possible incomparability of patients who receive different treatment modalities (ie, confounding) is adequately controlled for, observational studies could provide an alternative source of information.

A natural experiment design uses existing variation in treatment allocation (eg, due to practice variation). Natural experiments are observational studies in which treatment allocation is determined by factors outside the control of the investigators but also (to a large extent) independent of patient characteristics [6,7]. We assume the decisions regarding the treatment of distal radius fractures are largely influenced by the training of the treating surgeons. Since patients with a distal radius fracture generally visit the nearest hospital, treatment allocation is dependent on which surgeon is on call, which is likely independent on patient characteristics. Hence, the process governing treatment allocation arguably resembles that of randomization. Practice variation therefore provides an opportunity to conduct a natural experiment of the effect of operative versus nonoperative treatment of distal radius fractures. In order to further minimize the influence of patient characteristics on treatment decisions, a selection could be made of those patients for whom a panel of physicians disagree regarding the preferred treatment option (ie, for whom there clearly is a clinical equipoise). For these patients, both operative and nonoperative treatment of distal radius fractures are viable, and treatment choice is predominantly determined by personal or local preference.

This study is an international multicenter prospective observational cohort study for which patients will be identified after treatment has been initiated. Outcome data will be prospectively collected. Patients will be recruited from 5 hospitals in countries with a predominant preference for operative (Switzerland) and nonoperative treatment (the Netherlands).

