### Intervention

The decision whether operative or nonoperative treatment is chosen is left to the treating trauma surgeon as per the local standard of the participating hospital. Treatment will be initiated before the patient is approached for recruitment. Nonoperative treatment will consist of immobilization in a below the elbow cast for 4-6 weeks with or without prior closed reduction.

Operative intervention will be based on the treating surgeon’s experience and preference. It will consist of open reduction and internal plate fixation using volar, dorsal, spanning or a combination of plates, or reduction (open or closed) and fixation with an external fixator with or without Kirschner wires. The participating hospitals in Switzerland will use the 2.4-mm distal radius plate system (Arthrex) for internal plate fixation. Perioperative management including anesthesia, antibiotics, and thromboembolism prophylaxis will follow the national guidelines. Postoperative care and immobilization will be decided by the treating surgeon. When possible, functional aftercare without immobilization will be allowed. Physiotherapy will be provided according to the local standards.

All patients (operative and nonoperative) will be reviewed in the outpatient clinic at 6 and 12 weeks as well as 1 year after treatment or surgery. In addition, patients will be contacted by phone 2 years after treatment or surgery.

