#### Secondary Outcome Measures

##### Functional Outcome

Secondary functional outcome measures will include the PRWE at 1 year, Physical Activity Score for the Elderly, the Numerical Rating Scale for pain, and the EQ-5D-5L questionnaire. The Physical Activity Score for the Elderly is a questionnaire with multiple choice and open questions. The score combines information on household, leisure, and occupational activities. Based on duration, frequency, and intensity level of activities performed the previous week, a score is calculated ranging from 0 to 793, with higher scores reflecting more physical activity [10]. The EQ-5D-5L questionnaire is a questionnaire that measures general health status, with higher scores reflecting a better quality of life. It is based on 5 dimensions (mobility, self-care, usual activities, pain or discomfort, and anxiety or depression), which are rated on a scale with 5 levels. It also includes the EQ visual analogue scale for patients to state their self-rated health on a scale from 0 to 100, with 0 being the worst health imaginable [11]. The Numerical Rating Scale is a widely used scale to measure pain intensity, ranging from 0 (no pain) to 10 (worst pain imaginable) [4]. The living situation will be assessed at the first presentation, 6 weeks, 12 weeks, 1 year, and 2 years after injury. It will be defined as independent, independent with support from family, district nurse or similar, and nursing home. Range of motion of the wrist (dorsal extension, palmar-flexion, ulnar-, radial-abduction, pro-, and supination) as well as the finger-palm-distance will be assessed 12 weeks after injury. Additionally, the duration of surgery and the occurrence of intraoperative complications will be documented.

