##### Radiological Outcome

X-rays will be obtained as per standard hospital protocol at 6 and 12 weeks as well as 1 year after injury. The final radiological outcome will be determined 1 year after injury and will include union, radial inclination, volar tilt, carpal alignment, ulnar variance, and the presence and size of any step or gap in the articular surface.

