### Sample Size Calculation

This study will be a noninferiority study, for which we assume that conservative treatment in older patients with a distal radius fracture is noninferior to operative treatment. The reason for choosing a noninferiority design is as follows. Operative treatment for distal radius fractures inherently exposes patients to additional risks of operation-related complications and costs. This is not the case for conservative treatment. If the study would demonstrate that both treatments are equal with regard to the primary outcome, it would automatically imply that patients should be treated with the lesser invasive treatment of the 2 (in this case, conservative treatment).

The sample size is based on the minimal important clinical difference of the PRWE score, which is 11.5 points (with an average SD 14). Using the minimal important clinical difference (11.5 points) as the noninferiority margin, a statistical significance threshold (α) of 5%, and a power of 90%, 32 patients per group are needed [14]. Taking into account a 30% loss to follow-up (due to the considerable age of the included study population), a total of 92 patients will have to be included, with at least 46 patients in each treatment group.

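### Complications outside the four named ones are counted through a locally judged need for surgery, so ascertainment may differ between the arms

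*Protocol article*

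**What the plan says.** The Complications section of the protocol article gives the content of this secondary outcome: "They will include infection, nonunion, implant failure, complex regional pain syndrome, and any adverse event needing surgical intervention". It adds, "For patients treated surgically, the need for implant removal will also be recorded". Under Functional Outcome, "the duration of surgery and the occurrence of intraoperative complications will be documented". No other rule for counting complications is given.

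On who decides about surgery, the Intervention section says: "The decision whether operative or nonoperative treatment is chosen is left to the treating trauma surgeon as per the local standard of the participating hospital". The Study Design section gives the premise behind this, "We assume the decisions regarding the treatment of distal radius fractures are largely influenced by the training of the treating surgeons", and the choice of sites: "Patients will be recruited from 5 hospitals in countries with a predominant preference for operative (Switzerland) and nonoperative treatment (the Netherlands".

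Alignment is handled apart from complications. The Radiological Outcome section says: "The final radiological outcome will be determined 1 year after injury and will include union, radial inclination, volar tilt, carpal alignment, ulnar variance", and also lists articular step or gap. No condition on surgery is attached.

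The Sample Size Calculation section gives the reason for a noninferiority design: "Operative treatment for distal radius fractures inherently exposes patients to additional risks of operation-related complications and costs".

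**The concern.** An adverse event outside the four named ones has one stated route into the complication outcome: it must need surgery. Secondary displacement in a cast, tendon problems and nerve problems all depend on that route. Whether an event needs surgery is a judgement made at the treating hospital. Hospitals were chosen because they differ in how readily they operate on the initial fracture, and that difference largely sets the treatment arm. If the same difference carries over to later events, the probability that an event is counted depends on the exposure under comparison. That is differential ascertainment, and a larger sample does not remove it.

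The items recorded without this filter do not restore balance. Implant failure needs an implant, and implant removal and intraoperative complications can arise only in operated patients. With open fractures excluded, infection too will arise mainly after surgery. Nonunion and complex regional pain syndrome count in both arms without surgery.

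At stake is how the complication comparison is read. The plan's argument for the less invasive treatment appeals to the complication risk of surgery, so readers will set the complication results beside the primary result.

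**Working it through.** **The plan's own figure.** No figure is stated for complications. The only design calculation concerns the primary outcome: margin 11.5, SD 14, power 90%, and 5% taken as two-sided (2.5% one-sided). Then n = 2 × (1.960 + 1.282)² × 14² / 11.5² = 31.1, so 32 per group. Allowing for 30% loss, 32 / 0.70 = 45.7, so 46 per group and 92 in total. This reproduces the plan and does not depend on the complication definition.

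**Route into the complication outcome, from the text.**

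| Event | Named? | Needs surgery to count? | Recorded elsewhere? |
|---|---|---|---|
| Nonunion, complex regional pain syndrome | yes | no | union also under Radiological Outcome |
| Infection, implant failure | yes | no | – |
| Secondary displacement, malunion | no | yes | alignment at 1 year |
| Tendon or nerve problem | no | yes | only indirectly, through symptom and function scores |

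**Mechanism, with assumed values.** The documents give no rates, so these figures show only how the filter works. For the unnamed events,

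recorded rate = true rate × share judged to need surgery.

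Counts are out of 46 per arm.

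| True rate, nonoperative / operative | Share judged to need surgery, nonoperative / operative | Recorded rate | Count of 46 |
|---|---|---|---|
| 20% / 20% | 20% / 80% | 4% / 16% | 1.8 / 7.4 |
| 20% / 20% | 40% / 60% | 8% / 12% | 3.7 / 5.5 |
| 20% / 20% | 50% / 50% | 10% / 10% | 4.6 / 4.6 |
| 20% / 20% | 60% / 40% | 12% / 8% | 5.5 / 3.7 |
| 30% / 15% | 20% / 80% | 6% / 12% | 2.8 / 5.5 |

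For example, 0.20 × 0.20 = 0.04 and 46 × 0.04 = 1.8; 0.20 × 0.80 = 0.16 and 46 × 0.16 = 7.4.

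Equal shares give no distortion of the ratio, although half the events go uncounted in both arms. Unequal shares distort the comparison, and the direction follows whichever arm has the larger share. In the last row the order of the arms reverses. Nothing in the documents says which row is nearest the truth.

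**Films available for a remedy.** Table 1 marks X-rays at first presentation and 6 weeks only. The Radiological Outcome section has them at 6 weeks, 12 weeks and 1 year. The 6-week film stands in both places. The later films, on which the 1-year alignment record rests, are secure only once the two are reconciled. No post-reduction film is listed, and the Intervention section allows casts without prior reduction.

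**The case against.** Several points weigh against a stronger reading.

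- **The list may be open.** The wording introduces items that complications will include and does not expressly close the list. The data forms are not shown. This stands as a caution, but the text gives no other rule by which further events would count.
- **Malalignment is measured.** A reader might infer that unoperated failures of cast treatment are lost to the study. The documents do not support that: radiological alignment is recorded at 1 year regardless of surgery, and symptoms can show in the wrist score, pain, motion and quality of life. This stands in full. What remains is absence from the complication outcome.
- **The stated preferences concern initial treatment.** A reader might take it as the protocol's premise that readiness to reoperate differs by hospital. The Study Design and Intervention sections speak only of the initial choice. Carry-over to later events is plausible but inferred.
- **Need is not the same as having surgery.** True, but no independent judgement of need is described, so in practice it rests on local opinion.
- **The direction is not fixed.** A reader might infer that the definition will confirm the greater risk of surgery whatever the true rates. It need not: unoperated tendon and nerve events in the operative arm are hidden by the same filter, and equal readiness gives no distortion of the ratio. The noninferiority conclusion rests on the 12-week wrist score, and the plan does not make complications a test of its rationale.
- **Loss of reduction is hard to define here.** Without a scheduled post-reduction film, and with some fractures never reduced, change from the reduced position cannot be judged in every patient. This limits the remedy and is reflected in it.

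**Conclusion.** The concern holds in a limited form. Events outside the four named complications are counted through a locally judged need for surgery, in a study whose arms are formed largely by local readiness to operate on the initial fracture. Ascertainment of secondary displacement, tendon and nerve complications may therefore differ between arms.

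This rests on two assumptions: that the list works as the counting rule, since no other is given, and that local readiness to operate extends at least partly to later events. The size and net direction cannot be stated. The tabulated rates are assumptions and not estimates for this trial.

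The effect is confined to a secondary outcome. The primary outcome, the noninferiority decision and the sample size of 92 are untouched.

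**What to change.** In the Complications section:

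1. Count tendon complications and median-nerve complications in both arms, whether or not surgery follows.
2. Count secondary displacement in both arms, again whether or not surgery follows, by one prespecified radiographic criterion. Word it so that it can be judged on films already planned: first presentation and 6 weeks, with the later films added once the Radiological Outcome section and Table 1 are reconciled. It must not depend on a post-reduction film.
3. Report unplanned later surgery as a separate outcome instead of using need for surgery as the condition for counting an event.

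These changes concern measurement only and leave patient care as it is. The cost is a few extra data fields, completed from visits and films already planned, plus the work of agreeing the radiographic criterion. The complication rate may then look less favourable, particularly in the nonoperative arm.

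### The nonunion definition runs against its own scoring scale: a score of 6 or more marks healing, yet is labelled nonunion

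*Protocol article*

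**What the plan says.** All the relevant text is in the protocol article, Outcomes, under Complications and Radiological Outcome.

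- Definition: "Nonunion is defined as a Radius union scoring system score greater than or equal to 6". On timing: "It will be assessed 1 year after injury".
- Scale: "The RUSS score evaluates union on dorso-volar and lateral radiographs by assigning a score of 0 to 2 on each cortex".
- Lowest grade: "Zero points are given if the fracture line is visible with no callus".
- Middle grade: "1 point if a callus is present but the fracture line is still visible".
- Highest grade: "2 points if the fracture line is not visible and a bridging callus is present".
- Implants: "In surgically treated cases, where the cortex is not visible due to the implant, a score of 0 is given to that cortex". A reference is cited at this point (number 13 in the article).
- Where union is doubtful, a computed tomography scan is to be obtained. Patients with nonunion are then split into symptomatic and asymptomatic.

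The Radiological Outcome section lists union among the final 1-year outcomes but gives no definition of its own.

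**The concern.** Each extra point on this scale means more healing, but the definition attaches the nonunion label to the high end. Both cannot be right, and nothing elsewhere in the article corrects it. This is a decision threshold that will be applied to patients. A database programmed from the sentence as it stands would return well-healed fractures as complications and pass over fractures with no healing.

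Nonunion is a named complication, and the symptomatic/asymptomatic split is built on it. The Sample Size Calculation section justifies the noninferiority design partly by the extra complications of surgery, so complication counts will matter when the result is interpreted.

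A second issue appears once the direction is put right. A cortex hidden by an implant scores 0, the same as a cortex with no healing. Only operated patients can lose points this way, so the label could then depend on treatment as well as on healing.

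**Working it through.** **Inputs.** From the Complications section: 0, 1 or 2 points per cortex; two radiographic views; nonunion if the total is 6 or more; hidden cortex = 0. The number of cortices is not stated. I assume four (2 views × 2 cortices) and also check three and two. The article gives no score range or expected nonunion rate, so there is no figure of its own to reproduce. The sample-size inputs do not enter.

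**Step 1: the rule as written.** Total = sum over cortices; maximum = 2 × number of cortices.

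| Cortices scored | Maximum | All bridged | No healing | Patterns with total ≥ 6 |
|---|---|---|---|---|
| 4 (assumed) | 8 | 8: nonunion | 0: not nonunion | 15 of 81 |
| 3 | 6 | 6: nonunion | 0: not nonunion | 1 of 27 |
| 2 | 4 | 4: not nonunion | 0: not nonunion | 0 of 9 |

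With four cortices there are 3 × 3 × 3 × 3 = 81 possible patterns. The 15 labelled nonunion are those with the highest totals. The other 66 escape the label, including callus on every cortex with the line still visible (4 × 1 = 4) and no callus anywhere (0). With three cortices, only the fully bridged pattern is called nonunion. With two, the cut-off cannot be reached. The rule is reversed or unusable at every count. These are counts of possible patterns, not of expected patients.

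**Step 2: reversing the inequality (below 6 = nonunion, if 6 is the intended cut-off).** With four cortices and all of them visible, 8 becomes not nonunion and 0 becomes nonunion, which agrees with the scale.

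**Step 3: hidden cortices.** With four cortices and k hidden, a fully healed fracture scores at most 8 − 2k.

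| Hidden (k) | Best possible total | Rule as written (≥ 6) | Reversed rule (< 6) |
|---|---|---|---|
| 0 | 8 | nonunion | not nonunion |
| 1 | 6 | nonunion | not nonunion |
| 2 | 4 | not nonunion | nonunion |
| 3 | 2 | not nonunion | nonunion |

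Under the reversed rule, one hidden cortex leaves no slack: the other three must all be fully bridged, since 3 × 2 = 6. With two hidden, a healed fracture is always called nonunion. If only three cortices are scored, one hidden cortex is enough (6 − 2 = 4).

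**The case against.** The strongest reply is that this is a slip in one inequality, that it concerns a secondary complication, and that no surgeon would read a bridged fracture as a nonunion. The scale itself is clear, and a scan is available where union is doubtful. Much of this stands: a drafting slip is the likeliest explanation, and the trial's main conclusion does not rest on it. The scan does not repair the rule, however, because a plainly healed fracture raises no doubt and would still be coded by its score.

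Three stronger readings are tempting, and the documents do not support them.

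- A reader might infer that nearly every patient would be misclassified. That generalises from the two extreme patterns. A healed plated fracture with two hidden cortices (four assumed) scores at most 4 and is not mislabelled by the rule as written. The article gives neither the distribution of scores nor the number of hidden cortices, so no overall rate can be derived.
- A reader might infer that the 1-year union outcome is inverted as well. That follows only if union is taken as the complement of nonunion, which the article does not say.
- A reader might infer that the hidden-cortex rule will certainly bias the comparison against surgery. The rule comes with a citation and may belong to the published instrument; whether the cut-off already allows for it cannot be checked here. Operative treatment also includes external fixation with or without wires, so not every operated patient has a plate, and the scan may catch some unreadable cases. The supportable word is could.

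**Conclusion.** The contradiction is real and can be shown from the Complications section alone. The direction error needs no outside source and holds whatever the number of cortices: 8 of 8 is called nonunion with four, 6 of 6 with three, and with two the label can never apply. As written, the nonunion complication and its symptomatic/asymptomatic split are wrong. The 1-year union outcome is wrong too if it is taken as the complement. The 12-week PRWE outcome, the noninferiority margin and the sample size are untouched.

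The hidden-cortex point is conditional. It arises once the direction is corrected, and its size depends on how many cortices implants obscure, which is not given. Assuming four cortices and a cut-off kept at 6, a nonunion label for a healed fracture is possible with one hidden cortex and certain on the score with two. The scan provision covers this only in part, because the article does not say how its result alters the classification.

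**What to change.** **Required.** Reverse the inequality so that low scores mean nonunion: for example, below 6 if 6 is the intended cut-off. Check direction and cut-off against the cited scoring source. In the same sentence, state how many cortices are scored and the resulting range, and say whether the 1-year union outcome is the complement of nonunion.

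**Alongside it.** State that hidden cortices alone may not produce a nonunion label. One way is to report the published score and add a sensitivity analysis that treats implant-hidden cortices as not assessable. Say how a computed tomography result enters the final classification, in particular whether it overrides the radiographic score. Recording the number of hidden cortices per patient would show how much the rule matters.

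**Cost.** A few sentences in the outcome definition, the matching data dictionary entry and one small additional analysis. No extra patients or procedures are needed. Enrolment began in July 2023, so the first 1-year assessments fall around July 2024; the definition should be settled before those outcomes are coded, and any already coded should be re-derived from the cortex scores.

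### Scoring an implant-hidden cortex as 0 lowers the union score in operated patients only, so the between-arm nonunion comparison is partly an artefact of the implant

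*Protocol article*

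**What the plan says.** The Complications section of the Protocol article says that the RUSS "evaluates union on dorso-volar and lateral radiographs by assigning a score of 0 to 2 on each cortex". The grades run from least to most healed. At the bottom, "Zero points are given if the fracture line is visible with no callus"; at the top, "2 points if the fracture line is not visible and a bridging callus is present".

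For operated patients there is an extra rule: "In surgically treated cases, where the cortex is not visible due to the implant, a score of 0 is given to that cortex". One cut-off serves both arms: "Nonunion is defined as a Radius union scoring system score greater than or equal to 6". It is applied 1 year after injury. The section gives no category for a cortex that cannot be assessed, no rescaling, and no separate cut-off for operated patients. The next sentence offers a partial safeguard: "In case of doubt with regard to union, a computer tomography scan will be acquired".

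The Intervention section describes the operative arm as "open reduction and internal plate fixation using volar, dorsal, spanning or a combination of plates", or reduction with an external fixator, with or without Kirschner wires. The nonoperative arm receives a cast. Under Radiological Outcome, "The final radiological outcome will be determined 1 year after injury and will include union", without saying that the RUSS defines it. The Statistical Analysis section compares secondary outcomes between treatments by regression, adjusting for confounders, chiefly age and fracture type.

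**The concern.** A cortex that cannot be read is an unobserved value. The rule gives it the worst healing grade, and it can act in one arm only. Two wrists with the same healing, one in a cast and one plated, can therefore receive different totals and fall on different sides of the same cut-off.

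Adjustment for age and fracture type cannot remove this, because the error is produced by the treatment. The planned multiple imputation does not reach it either: a recorded 0 is not a missing value.

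At stake is the comparison of nonunion, a listed complication, and also the comparison of radiological union if that is taken from the RUSS. The noninferiority rationale in the Sample Size Calculation section rests on the extra complications of surgery, so a complication whose measurement depends on the implant bears on how the study is read.

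**Working it through.** The article gives no event rate, power or expected score for union or nonunion, so there is no figure of the plan's own to reproduce. The sample size (32 per group, 46 after 30% loss, 92 in total) is for the primary PRWE outcome and plays no part here.

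**Inputs from the Complications section:** 0 to 2 points per cortex; hidden cortex = 0; cut-off 6 in both arms.

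**Assumptions, not in the documents:** four cortices (two views, two cortices each); each visible cortex scores 2 with probability p and otherwise 1, independently; the number of cortices hidden (0, 1 or 2).

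**Step 1: attainable maximum** = 2 × number of visible cortices.

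| Hidden | Visible | Maximum | Needed to reach 6 |
|---|---|---|---|
| 0 | 4 | 8 | mean of 6/4 = 1.5 per visible cortex |
| 1 | 3 | 6 | 6/3 = 2, so every visible cortex fully bridged |
| 2 | 2 | 4 | 6/2 = 3, impossible |

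**Step 2: chance of scoring below 6 at identical healing.**

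- None hidden: at least three of four cortices must score 1, so P = 4p(1−p)³ + (1−p)⁴. At p = 0.90 this is 4 × 0.9 × 0.001 + 0.0001 = 0.0037.
- One hidden: P = 1 − p³.
- Two hidden: P = 1.

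| p | None hidden | One hidden | Two hidden |
|---|---|---|---|
| 0.90 | 0.4% | 1 − 0.729 = 27% | 100% |
| 0.95 | 0.05% | 1 − 0.857 = 14% | 100% |
| 0.99 | under 0.01% | 1 − 0.970 = 3% | 100% |
| 1.00 | 0% | 0% | 100% |

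Allowing a small chance of a zero on a visible cortex leaves the pattern unchanged. With probabilities 0.02/0.08/0.90 for scores 0/1/2, the chance of reaching 6 is 0.98, 0.73 and 0 with none, one and two hidden. With 0.05/0.15/0.80 it is 0.91, 0.51 and 0.

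**Step 3: direction.** Take p = 0.90 and one hidden cortex.

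- Cut-off as written (6 or more = nonunion): counted nonunion is 1 − 0.0037 = 99.6% with all cortices visible and 1 − 0.271 = 72.9% with one hidden. The rule lowers it in the operative arm.
- Cut-off reversed (below 6 = nonunion): 0.4% against 27.1%. The rule raises it in the operative arm.

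The gap is 26.7 percentage points in either case (27.1 − 0.4); only its sign changes. Settling the direction of the inequality does not remove it.

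**The case against.** Five points can be made for the plan.

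1. *The rule is cited to a source and may be the published convention.* On the four-cortex assumption, a fully bridged fracture with one hidden cortex scores exactly 6, so the cut-off may already allow for one obscured cortex. The documents neither confirm nor exclude this. It would explain the rule, but it would not make the scores comparable: one arm would still need every visible cortex bridged, and the other would not.

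2. *The size is unknown.* This stands. The number of cortices, p, independence and the number hidden are all assumed. Assessment is at 1 year, when p may be close to 1. An external fixator may hide nothing, implants may have been removed (the need for removal is recorded), and combined plates are one option among several, with no frequency given.

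3. *CT may resolve doubtful cases.* An unreadable cortex is a natural reason for doubt, and the CT sentence directly follows the zero rule. But the article does not define doubt, does not say that a hidden cortex triggers a CT, and does not say whether score or CT prevails. A reader might infer that the score always classifies the patient regardless of CT, or that plated patients will have more CTs. The text establishes neither.

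4. *Healed plated wrists are not counted as nonunion under the present text.* This also stands. A reader might infer that they are, but that requires the cut-off to be reversed first, and then either incomplete bridging or at least two hidden cortices.

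5. *Only secondary outcomes are involved, and the Radiological Outcome section does not tie union to the RUSS.* Correct, and it limits the scope of the point.

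**Conclusion.** The point holds as a treatment-dependent measurement rule for a secondary outcome. It follows from the text alone that at equal healing an operated patient's total is equal or lower, never higher, and that a common absolute cut-off then classifies the arms on different attainable scales. Age and fracture-type adjustment and the undefined CT clause do not remove this.

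The direction cannot be fixed until the cut-off is reconciled with the scoring. The size cannot be taken from the documents: the bias is nil where no cortex is hidden. On the four-cortex assumption, one hidden cortex shifts the chance of falling below 6 by anything from 0 to about 27 percentage points for p between 1 and 0.90, and two hidden cortices put 6 out of reach. A reader might take 27% or 100% as the expected error in this study; the documents do not support that.

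The primary PRWE outcome and the sample size are untouched.

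**What to change.** Amend the outcome definition as follows, alongside the separate reconciliation of the cut-off's direction:

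- Record an implant-obscured cortex as not assessable instead of 0.
- Compare union or nonunion between arms on the visible cortices, as points divided by the attainable maximum, and state the rounding for each number of visible cortices. For example, 6 of 8 is 75%. With two visible cortices this is 3 of 4, but with three it is 4.5 of 6, which has to become 4 (67%) or 5 (83%). The fraction cannot be identical throughout, so the choice should be written down in advance.
- Report by arm the number of non-assessable cortices and the number of CTs.
- State whether a CT result already obtained overrides the score.
- Say whether radiological union is taken from the RUSS.
- Show the original published scoring alongside as a sensitivity analysis.

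The cost is a few sentences and a recode of the RUSS field, with no added visit or imaging. The downside is that the rescaled score modifies the cited instrument, which is why the original scoring should stay in the report.
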